## Abstract

**Background:**

Gestational diabetes mellitus (GDM) is increasing worldwide and has been associated with adverse perinatal outcomes and high risk for chronic disease both for the mother and for the child. Physical exercise is feasible for diabetic pregnant women and contributes to better glycemic control and to a decrease in adverse perinatal outcomes. However, there are no randomized controlled trials (RCT) assessing the effects of aquatic physical exercise on GDM control and adverse maternal and fetal outcomes.

**Methods/Design:**

An RCT will be conducted at Instituto de Medicina Integral [name] (IMIP), Brazil. A total of 72 pregnant women will be studied; 36 gestational diabetics will undergo an aquatic physical exercise program in a thermal pool, 3 times per week over 2 months. The primary endpoint will be glucose level control and use of insulin; secondary endpoints will be the following maternal and fetal outcomes: weight gain during pregnancy, blood pressure, pre-eclampsia diagnosis, intrauterus growth restriction, preterm birth, Cesarean section, macrosomia and maternal or neonatal intensive care admission. Endpoints between intervention and control group will analyzed by t test for unpaired data and χ^2^ test, and the level of significance will set at <0.05.

**Discussion:**

The physical proprieties of water make aquatic exercises ideal for pregnant women. An aquatic physical exercise program developed for GDM women will be trialed in a thermal pool and under the supervision of physiotherapist to ensure compliance. It is expected that this study will provide evidence as to the effect of aquatic physical exercise on GDM control.

**Trial registration:**

ClinicalTrial.gov, NCT01940003.

## Background

The prevalence of gestational diabetes mellitus (GDM), defined as glucose intolerance first diagnosed during pregnancy, is increasing worldwide concurrent with the rise in obesity and type 2 diabetes [1]. According to the International Association of Diabetes and Pregnancy Study Groups (IADPSG) and based on the new screening criteria for GDM from the Hyperglycemia and Adverse Pregnancy Outcomes (HAPO) study, the incidence of GDM has reached almost 18% [2]. GDM has been associated with significant rates of adverse perinatal outcomes [3]. Both GDM women and their offspring also have a high risk of developing obesity, type 2 diabetes and metabolic disease throughout life [4].

Physical activity improves glucose utilization by increasing insulin sensitivity [5]. Physical activity can delay the progression of impaired glucose tolerance in type 2 patients and also contributes to overweight/obesity control, reduction of medication dose and cardiovascular risk factors [6]. Physical exercise is safe for pregnant women and has been recommended at a level of 30 minutes or more on most days of the week, as a helpful adjunctive therapy for GDM [7,8]. Physical activity during pregnancy may contribute to improved levels of maternal glucose tolerance and help prevent GDM [9]. However, a Cochrane systematic review concluded that there was insufficient evidence to recommend, or advise against, diabetic pregnant women enrolling in exercise programs [10].

The physical properties of water make aquatic exercise ideal and safe for pregnant women [11]. Aquatic exercise has been recommended during pregnancy due to it having less impact on articulation, and its ability to increase amniotic fluid diuresis and decrease edema, blood pressure and back pain [12,13]. Furthermore, aquatic exercise during pregnancy may decrease maternal stress, discomfort and improve health-promoting behaviors [14,15]. However, there is insufficient evidence on aquatic exercise due to poor methodological and reporting quality and heterogeneity of non-randomized clinical trials [10,16]. Specifically in relation to GDM, there are no clinical trials testing aquatic exercise as an adjunctive treatment.

### Hypothesis

Aquatic physical exercise is feasible for diabetic pregnant women and contributes to better glycemic control and decreases adverse perinatal outcomes.

### Research goals

To verify the efficacy of an aquatic physical exercise program on GDM control and adverse maternal and fetal outcomes.

## Methods/Design

### Setting and recruitment

The study will take place at Instituto de Medicina Integral [name] (IMIP), Brazil. IMIP is a reference hospital in the Northeast Brazil for mother and child care, and performs about 6,000 deliveries per year. Recruitment will focus on GDM women diagnosed at IMIP or referred to the center for treatment; this is about 50 GDM women per month.

### Participant selection

Obstetrical staff will identify pregnant women recently diagnosed with GDM; following IMIP guidelines, a 75 g oral glucose tolerance test (OGTT) is routinely performed between the 24th and 28th gestational week. These patients will be approached by a member of the study team and permission will be sought after an explanation of the study goals. GDM women will be considered eligible for enrollment if they fulfill all the inclusion criteria and none of the exclusion criteria. Interested patients will be invited to sign a written informed consent.

### Study design

This is an RCT to assess the effects of a 2-month water exercise program on GDM control and perinatal outcomes.

### Inclusion criteria

GDM diagnosis will be based on the IADPSG HAPO study (2 h, 75 g OGTT: fasting glucose ≥92 mg/dl or a 1-h result of ≥180 mg/dl, or a 2-h result of ≥153 mg/dl) [17]. Subjects must be aged 18 to 35 years and physically inactive (<150 minutes per week based on International Physical Activity Questionnaire) [18].

### Exclusion criteria

These are: multiple pregnancy, cervical incompetence, placental dysfunction, intrauterus growth restriction, preterm labor, suspicion of fetal suffering, heart or pulmonary insufficiency and blood hypertension.

### Sample size

The sample size was calculated with the aim of reducing glucose levels by 20% on average in the intervention group. A power of 80% and a level of significance of 5% was accepted, and thus the calculated sample size in each arm was 30 patients. Assuming a dropout of 20%, 72 pregnant women will be included in the study.

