### Randomization

Randomization will be performed according to a computed-generated allocation (http://www.randomized.com). Pregnant women will be assigned, in a 1:1 ratio, to exercise intervention or usual care. Blinding of the study to the randomization arm is not possible due to the nature of intervention.

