### Analyses

Maternal and fetal characteristics of the study sample will be presented by group, intervention and control in terms of mean and SD. For group comparisons of glucose levels and perinatal variables, continuous and nominal data will be analyzed by t test for unpaired data and χ^2^ tests, respectively. Data will be analyzed using the intention-to-treat principle. Statistical analysis will be performed with STATA version 3.1 and the level of significance will set to <0.05.

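### The 72 women allow for a dropout of 16.7%, not the stated 20%, because the allowance was added to the 60 evaluable women instead of being taken from those enrolled (minor)

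*Protocol article*

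**What the plan says.** The Sample size section of the protocol article builds the number in two steps. The first step gives the evaluable size. The aim is "reducing glucose levels by 20% on average in the intervention group", "A power of 80% and a level of significance of 5% was accepted", and as a result "the calculated sample size in each arm was 30 patients". The second step allows for losses: "Assuming a dropout of 20%, 72 pregnant women will be included in the study".

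The abstract repeats the total and gives the exercise arm: "A total of 72 pregnant women will be studied; 36 gestational diabetics will undergo an aquatic physical exercise program". The Randomization section fixes equal allocation: "Pregnant women will be assigned, in a 1:1 ratio, to exercise intervention or usual care". The Analyses section names the test: "continuous and nominal data will be analyzed by t test for unpaired data and χ^2^ tests, respectively". Nowhere does the article correct or qualify the 72.

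**The concern.** Three stated figures do not fit together: 30 evaluable women per arm, a 20% dropout, and 72 women enrolled. A dropout rate is ordinarily a share of the women enrolled, so the evaluable number should be divided by 0.8. Here it appears to have been multiplied by 1.2.

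What is at stake is modest but concrete. Readers will use this sentence to judge whether losses stayed within plan. As it stands, a trial that loses exactly the planned 20% ends with fewer evaluable women than the same section says it needs.

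**Working it through.** **Inputs, all from the protocol article**

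- Evaluable size: 30 per arm, 60 in total (Sample size)
- Dropout: 20% (Sample size)
- Enrolment: 72 in total (Sample size and abstract), 36 of them in the exercise arm (abstract)
- Allocation: 1:1 (Randomization)
- Power 80%, significance level 5%, sidedness not stated (Sample size)
- Test: unpaired t test for continuous data (Analyses)
- SD and control mean of glucose: not given

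**Step 1. Reproduce the plan's figure.** Adding the dropout rate to the evaluable number, n × (1 + d):

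- 60 × 1.2 = 72 in total
- 30 × 1.2 = 36 per arm

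Both match the article exactly.

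**Step 2. Apply 20% as a loss from those enrolled.**

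- 72 × 0.8 = 57.6 women remain, so 57 or 58
- 36 × 0.8 = 28.8 per arm, against the stated 30

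**Step 3. Dropout that 72 can absorb.**

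- 72 − 60 = 12 women
- 12/72 = 16.7%

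**Step 4. Enrolment that keeps 60 after a 20% loss, n/(1 − d).**

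- 60/0.8 = 75 in total
- 30/0.8 = 37.5, rounded up to 38 per arm, or 76 in total

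The gap to 72 is 3 or 4 women.

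**Step 5. Effect on power (conditional).** The 30 per arm cannot be re-derived from a 20% reduction without an SD and a control mean. I therefore assume that 30 per arm gives 80% power, find the standardized difference δ that this implies, and ask what power remains at the smaller size.

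Normal approximation, two-sided 5%:

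- δ = (1.960 + 0.842) × √(2/30) = 0.723
- power at n per arm = Φ(δ × √(n/2) − 1.960)
- at n = 28.8: 0.723 × √14.4 = 2.745, and Φ(2.745 − 1.960) = 78.4%

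| Assumption | Power at 28.8 per arm | Power at 29 per arm |
|---|---|---|
| 30 gives exactly 80%, two-sided, normal approximation | 78.4% | 78.7% |
| 30 gives exactly 80%, two-sided, noncentral t | 78.3% | 78.6% |
| 30 gives exactly 80%, one-sided 5%, normal approximation | 78.6% | 78.8% |
| 30 was rounded up from 29.01, two-sided, normal approximation | 79.7% | just under 80% (79.99%) |

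At 28.8 per arm the loss runs from 80 − 79.7 = 0.3 points to 80 − 78.3 = 1.7 points.

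**The case against.** The division itself is hard to dispute. The objections concern what follows from it.

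**The 20% could mean 20% of the completers.** On that reading 12/60 = 20% and 72 is right. The article does not say so, and a dropout rate is normally read as a share of those enrolled. If this was the intent, the sentence still has to say it.

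**A dropout need not be a lost outcome.** The article does not define the term. The Analyses section specifies intention to treat, and the section on post-randomization evaluations has the same hospital staff managing both arms, with capillary glucose measured at each visit. A woman who leaves the pool sessions may still contribute glucose data. This is a fair point: the shortfall arises only if more than 16.7% of the women are lost to the analysis. It does not rescue the sentence, because adding an allowance to the evaluable number already treats dropouts as lost. The same section also requires at least five glucose determinations per woman, which an early leaver may not supply.

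**The power consequence is small and cannot be verified.** This stands. A reader might infer that the trial fails to deliver its 80% power in any meaningful sense. The article does not support that: it lacks the SD, control mean and sidedness needed to check the power at 30 per arm, and under the assumptions above the loss is under 2 points. Nor should one round down to 28 per arm, where power would be about 77.1%. That is 56 women, a loss of 16/72 = 22.2%, which is more than the plan assumes.

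**Conclusion.** Wrong as written, and minor. On the ordinary meaning of dropout, 72 women allow for 16.7% and not 20%. At 20% about 57 or 58 women remain, one or so per arm below the stated 30. This conclusion rests only on figures printed in the Sample size section.

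The statement on power is weaker and conditional. If 30 per arm gives 80%, two-sided power at 20% dropout lies between about 78% and just under 80%. The lower end applies if 30 gives exactly 80%, the upper end if 30 was rounded up from just over 29. Neither case can be confirmed from the article. The error affects neither the choice of analysis nor the risk of bias.

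**What to change.** Restate the one sentence in the Sample size section in one of these ways:

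- Keep 72 and say that it allows for a dropout of about 16.7% (12 of 72).
- Keep 72 and 20%, and say that about 58 evaluable women are then expected, with power slightly below 80%. The power figure should be recomputed from the sponsor's original inputs and not copied from the conditional range above.
- If enrolment can be extended, keep 20% and 60 evaluable women and raise the total to 75, or 76 with equal arms. The abstract's 72 and 36 would then change too.

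Do not add a standardized target. The two-sided t-test calculation implies a difference of about 0.74 SD, but that value is back-calculated from 30 per arm and 80% power. The stated design basis is a 20% mean reduction in glucose.

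Either of the first two options costs one sentence. The first states a smaller loss allowance and the second a slightly less favourable power. The third costs 3 or 4 more participants.

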### Primary endpoint

Glucose control will be considered as fasting capillary glucose levels of 95 mg/dl or less and postprandial levels of 120 mg/dl according to American Diabetes Association (ADA) guidelines [8]. The mean value of capillary glucose levels (fasting and postprandial) and the number of measurements above recommended values (ADA) will be compared between the groups.

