### Post-randomization evaluations

To ensure that similar guidelines for GDM clinical treatment are maintained for the two groups, IMIP obstetrical staff will undertake the ongoing GDM management of all trial participants for the period of the study. Participants are usually clinically evaluated at a minimum of every 2 weeks depending on GDM control, according to the IMIP guidelines for GDM. A capillary glucose test is performed at each clinical visit.

Self-monitoring of fingertip capillary blood glucose will be performed after overnight fasting, 2 h after breakfast, 2 h after lunch, and 2 h after dinner. The capillary glycemic profile will be determined every other week until 34 weeks of gestation, and weekly thereafter. All women will receive instructions to measure capillary glycemia with an Accu-Chek Advantage glucose meter (Roche Diagnostics, Indianapolis, IN, USA) and glucose blood strips. Insulin will be introduced when more than two glucose measurements are above the recommended value.

The mean capillary glucose profile will be analyzed post intervention (minimum of five determinations per woman). Insulin or oral hypoglycemia will be compared between the two groups.

All pregnant women will wear a pedometer (Yamax Digi Walker SW-200, Tokyo, Japan) during the whole study. Pedometer readings will provide a measure of physical activity to compare both groups.

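### The abstract and the Primary endpoint section disagree on whether insulin use is primary, and two to four results could carry the primary label, each at 0.05.

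*Protocol article*

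**What the plan says.** All references are to the protocol article.

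- **Abstract, Methods/Design:** "The primary endpoint will be glucose level control and use of insulin".
- **Primary endpoint:** control is first defined by a fasting and a postprandial threshold. The section then compares the mean capillary glucose (fasting and postprandial) "and the number of measurements above recommended values (ADA) will be compared between the groups". Insulin does not appear, and no comparison of women meeting the thresholds is stated.
- **Secondary endpoints:** neither insulin nor any other glucose-lowering drug is listed.
- **Post-randomization evaluations:** a single mean glucose profile is to be analyzed after the intervention, and "Insulin or oral hypoglycemia will be compared between the two groups". That comparison is called neither primary nor secondary.
- **Sample size:** the aim is "reducing glucose levels by 20% on average in the intervention group", and "A power of 80% and a level of significance of 5% was accepted". The section does not say whether the glucose level is fasting, postprandial or pooled.
- **Analyses:** t tests and chi-square tests are used, and "the level of significance will set to <0.05".

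**The concern.** The primary endpoint decides what the trial can claim, and this article gives two versions of it. Insulin use is primary in the abstract and absent from the section that defines the primary endpoint. Elsewhere it is compared without a label and together with oral agents. Within the Primary endpoint section itself, more than one comparison shares the label, and the text does not say which one the sample size was built on.

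The trial is unblinded and has 72 women. If the wording stays as it is, a claim that aquatic exercise improves control of gestational diabetes could rest on whichever result falls below 0.05. Insulin use could be counted as primary or left out once the data are known. The error rate of such a claim would be above 5%.

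**Working it through.** **1. How many results can be called primary.** The bracketed mention of fasting and postprandial in the Primary endpoint section can mean one pooled mean or two means. The single mean profile in Post-randomization evaluations favors pooling but does not settle it.

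| Reading | Without insulin | With insulin (abstract) |
|---|---|---|
| Pooled mean + count of high readings | 2 | 3 |
| Fasting mean + postprandial mean + count | 3 | 4 |

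The range is therefore two to four.

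**2. The plan's own figure.** The article says that "the calculated sample size in each arm was 30 patients". It gives no SD and no control mean, so 30 cannot be reproduced forwards. Solved backwards, with a two-sided test assumed because sidedness is not stated:

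d = (1.960 + 0.842) × √(2/30) = 0.723

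A 20% reduction then implies an SD of 20/0.723 = 27.6% of the control mean. The calculation is for a single comparison of glucose means at an undivided 0.05. The total of 72 follows as 2 × 30 × 1.2.

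**3. Error rate if any one result suffices.** For k independent tests at 0.05 the rate is 1 − 0.95^k:

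- k = 2: 1 − 0.9025 = 9.75%
- k = 3: 1 − 0.8574 = 14.3%
- k = 4: 1 − 0.8145 = 18.5%

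The results are correlated. The means and the count come from the same readings, and starting insulin depends on readings above target. The article gives no correlation, so a range is assumed. Test statistics were simulated as Z_j = √ρ·G + √(1−ρ)·E_j with G and E_j standard normal (500,000 draws), counting a draw when any |Z_j| > 1.96.

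| Correlation ρ | 2 results | 3 results | 4 results |
|---|---|---|---|
| 0 (formula) | 9.75% | 14.3% | 18.5% |
| 0.3 | 9.5% | 13.6% | 17.3% |
| 0.5 | 9.1% | 12.6% | 15.5% |
| 0.7 | 8.3% | 11.0% | 13.0% |
| 0.9 | 7.0% | 8.4% | 9.4% |

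Every cell is above 5%.

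**4. What happens to power.** This depends on the success rule, which the article does not state. Each test is taken to have 80% power at 0.05.

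- *Any one suffices:* power for the mean-glucose test stays at 80%. Only the error rate is affected.
- *All must be significant:* the error rate stays at or below 5%. With independent results, power is 0.8² = 64% for two and 0.8⁴ = 41% for four. At correlation 0.9 it is 75% and 70%.
- *0.05 divided equally:* the error rate holds. Power at 30 per arm is 71% for two tests and 62% for four.

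**5. Insulin use.** The article gives no rates, so these are assumed, with the intervention halving the control rate. At 30 per arm (normal approximation), for 50% against 25%:

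- pooled rate 0.375, null SE = √(2 × 0.375 × 0.625/30) = 0.125
- alternative SE = √((0.25 + 0.1875)/30) = 0.121
- z = (0.25 − 1.960 × 0.125)/0.121 = 0.04, so power is about 52%

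The same steps give 39% for 40% against 20%, and 28% for 30% against 15%.

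**The case against.** The strongest reply has three parts.

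*The article condenses a fuller protocol, and a statistical analysis plan may exist.* A multiplicity procedure or a success rule is commonly kept there, so its absence here is not in itself an error. That stands. It does not cover the contradiction on insulin, which lies between the article's own abstract and body, nor the several comparisons placed under the primary label.

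*The Analyses section states a significance level, not that a single p-value below it establishes efficacy.* That is also right, and the error rates above are therefore conditional on an any-one rule.

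*The sample size section claims power for a glucose level only.* Correct. It makes no promise about the count or insulin use that could be broken.

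Three stronger readings are tempting and are not supported:

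- A reader might infer that there are at least four primary results. Four is the top of the range: it needs the means split and insulin added from the abstract.
- A reader might infer that the error rate is about three times 5%. That requires four results with correlation of about 0.5 or lower, and results drawn from the same readings may well be more closely correlated.
- A reader might infer that the 5% level and the 80% power both fail. They do not fail together. Under an any-one rule, power for mean glucose is untouched; it falls only if all results are required or the level is divided.

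Nor does the section on post-randomization evaluations widen the primary endpoint to oral agents, since it attaches no label to that comparison.

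**Conclusion.** The concern holds in limited form. Insulin use is primary in the abstract, missing from both endpoint sections, and compared without a label elsewhere. The Primary endpoint section adds two or three glucose comparisons of its own, and the sample size does not say which glucose measure it concerns.

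Two to four results can thus be called primary. If any one suffices, the false-positive rate is about 7% to 10% for two and about 9% to 18.5% for four. These figures assume two-sided tests at 0.05 and a common correlation between 0.9 and 0, neither of which the article gives. The excess over 5% does not depend on the count chosen, but it does depend on the any-one rule.

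On power, only a narrow statement stands: the 80% relates to one mean-glucose comparison, cannot be verified without an SD, and gives no basis for the count or insulin use.

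**What to change.** 1. Reconcile the abstract, Primary endpoint, Secondary endpoints and Post-randomization evaluations on insulin use: give it one status and one definition, stating whether oral agents are included.
2. Name one primary variable, and state how fasting and postprandial readings enter it. Mean capillary glucose is the natural candidate because the sample size already concerns a glucose level, but the choice is the sponsor's.
3. Say in Sample size that the calculation concerns that variable, with the SD and control mean used. Test it alone at two-sided 0.05.
4. Test the other glucose results and glucose-lowering drug use in a stated fixed order, or report them as supportive with 95% confidence intervals and no claim of significance.

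Recruitment is already open, so the change should be dated and made before any comparison by arm is seen. If mean glucose is kept as primary, the cost is wording in the protocol, the analysis plan and the registration, with no added women or visits. If the count or insulin use is chosen instead, the sample size has to be recalculated. The downside is fewer routes to a positive claim.
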